## Abstract

**Background:**

Several studies have reported that the triangulating stapling method decreases the incidence of anastomotic stricture after esophagectomy. Our previous randomized controlled trial, however, could not confirm the superiority of the triangulating stapling (TS) method over the circular stapling (CS) method in terms of postoperative anastomotic stricture rate. Recently, the functional end-to-end stapling (FEES) method for cervical anastomosis after esophagectomy was developed, and lower anastomotic stricture rates with FEES have been reported than for our previously experienced anastomotic methods. To investigate the optimal anastomotic method, we now compare the TS method with the FEES method for cervical anastomosis regarding decrease in anastomotic stricture after esophagectomy for thoracic esophageal cancer.

**Methods:**

This is a randomized, single-center clinical trial designed to examine the superiority of the FEES method over the TS method for esophageal cancer patients. The primary endpoint is reduction of anastomotic stricture of cervical esophagogastric anastomosis within 12 months after esophagectomy. Secondary endpoints include overall postoperative morbidity within the first 12 months after esophagectomy, incidence of anastomotic leakage, aspiration pneumonia, or reflux esophagitis, and quality of life assessment as measured by the FACT-E at 12 months after esophagectomy. The incidence rate of anastomotic stricture of the TS method was 20% and this rate of the FEES method was estimated to be 4% in our preliminary study. We calculated sample size with a beta error of 0.20 and an alpha error of 0.05. We have been enrolling 125 patients in this trial to either the TS group or the FEES group since January 2017.

**Discussion:**

This study should help to define the optimal anastomotic method for cervical esophagogastric anastomosis after esophagectomy in patients with esophageal cancer.

The FEES method, if proven to be superior to the TS method, can be implemented routinely for esophageal cancer patients with gastric-conduit reconstruction after esophagectomy.

**Trial registration:**

University Hospital Medical Information Network Clinical Trial Registry (UMIN 000025632). Registered on 13 January 2017.

**Electronic supplementary material:**

The online version of this article (10.1186/s13063-019-3201-2) contains supplementary material, which is available to authorized users.

## Background

After subtotal esophagectomy for esophageal cancer, anastomosis of the cervical esophagus and other organs is needed, which connects the adjacent digestive tract to repair digestive function. Reconstruction using a gastric conduit is the most common procedure after esophagectomy, although various other anastomotic techniques have been investigated [1–4]. In spite of recent advances in esophagectomy and management after surgery for esophageal cancer, the optimal anastomotic method has not yet been established. Moreover, complications related to anastomosis remain a major concern for surgeons. Our previous randomized controlled trial (RCT) compared the circular stapling (CS) and triangulating stapling (TS) methods in cervical esophagogastric anastomosis, but it could not demonstrate the superiority of the TS method over the CS method [4]. Complications of esophagogastric anastomosis remain frequent and the improvement of anastomosis techniques is thought to reduce complications.

In 1968, Steichen first reported functional end-to-end anastomosis (FEEA) using linear staplers [5]. To date, the FEEA technique has been increasingly adopted in anastomosis of the colon and the intestine. In esophagogastric anastomosis, Collard first reported side-to-side anastomosis using a linear stapler [6], this functional end-to-end stapling (FEES) method and is also known as the “modified Collard anastomosis” [7]. Recently, the FEES method after esophagectomy has been introduced in many facilities. We also have adopted the FEES method for esophagogastric anastomosis (Fig. 1). Theoretically, the FEES method produces a larger anastomosis than other anastomotic methods [6], so we postulate that the incidence of anastomotic stricture for cervical esophagogastric anastomosis using the FEES method should be lower than that using the TS method. No RCTs have yet compared the FEES and TS methods for cervical esophagogastric anastomosis after esophagectomy. To clarify the efficacy of the FEES method, a RCT comparing the FEES method and popular TS method is desirable in esophagogastric anastomosis. Our RCT will compare anastomotic stricture rate and the other postoperative complication rates of the FEES and TS methods for esophagectomy.

**Fig. 1 Fig1:**
[figure not shown]
Functional end-to-end stapling for a cervical esophagogastric anastomosis using the linear stapler: **a** The first firing of the stapler was applied to the posterior wall of the remnant esophagus and the gastric conduit after insertion of two suspension sutures in an inverted fashion. **b** Schema after the first firing of the stapler. **c** The second firing of the stapler was applied in an everted fashion

## Methods

### Study objectives

This prospective, single-center, phase III trial aims to demonstrate the superiority of the FEES method over the TS method for cervical esophagogastric anastomosis concerning reduction of anastomotic stricture.

### Study setting

This is a **s**ingle-institution, randomized, phase III study.

### Study endpoints

The primary endpoint is the incidence of anastomotic stricture within 12 months after esophagectomy. Secondary endpoints include any incidence of anastomotic leakage, aspiration pneumonia, or reflux esophagitis, overall postoperative morbidity within 12 months after surgery, and quality of life (QOL) evaluation according to the Functional Assessment of Cancer Therapy-Esophageal (FACT-E) version 4.0 12 months after surgery [8]. The Comprehensive Complication Index (CCI) is also calculated as the sum of all complications [9].

### Sample size calculation

Our previous study described a stricture rate of 18% in patients who underwent the TS method [4]. However, as a result of continuing the research involving an additional number of cases, the incidence rate of anastomotic stricture of the TS method was adjusted to 20%.

We therefore estimate an incidence rate of 20% in the TS group. This rate of the FEES method was estimated to be 4% in the retrospective study. We hypothesize a reduction in stricture risk from 20 to 4%, and this reduction rate to be a clinically profitable figure. A sample size of 59 patients per arm is needed in this study with a beta error of 0.20 (power 80%) and a one-sided alpha error of 0.05%. Anticipating follow-up loss, we will recruit a total of 125 patients for this trial (Fig. 2).

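### The sample-size section prints the one-sided alpha as 0.05% where the abstract has 0.05; 59 per arm fits a 5% level, and its sidedness and test need to be stated

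*Protocol article*

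**What the plan says.** Protocol article, *Sample size calculation*:

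- Control (TS) rate: "We therefore estimate an incidence rate of 20% in the TS group".
- FEES rate: "This rate of the FEES method was estimated to be 4% in the retrospective study".
- Power and significance level: "a beta error of 0.20 (power 80%) and a one-sided alpha error of 0.05", with a percent sign printed directly after the last figure, so an alpha of 0.05%, or 0.0005.
- Result: "A sample size of 59 patients per arm is needed in this study".
- Recruitment: "Anticipating follow-up loss, we will recruit a total of 125 patients for this trial".

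Protocol article, *Abstract, Methods*, on the same calculation: "We calculated sample size with a beta error of 0.20 and an alpha error of 0.05". Here there is no percent sign and no sidedness.

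Protocol article, *Data collection and statistics*: chi-square, Fisher's exact and Mann-Whitney tests, and a 95% confidence interval for the treatment effect. This section gives neither a significance level nor a sidedness.

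**The concern.** The two statements of alpha differ by a factor of 0.05 / 0.0005 = 100, and nothing in the article explains a level of 0.05%. Alpha, power, the two rates and the sample size are tied together by arithmetic, so at most one of the two levels can belong with 59 per arm.

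The error rate concerns the primary superiority question. The statistics section does not restate it, so a reader who looks for it in the methods text finds 0.05%. Deleting the percent sign also leaves a gap. The sample-size section says one-sided, the abstract is silent, and a 95% interval corresponds to a two-sided 5% test. For a borderline result, the sidedness and the test could decide whether superiority is declared.

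**Working it through.** **Inputs** (*Sample size calculation*; allocation from *Randomization*): p1 = 0.20, p2 = 0.04, difference d = 0.16, mean rate 0.12, 1:1 allocation, power 0.80 (z = 0.8416), n = 59 per arm. The article does not name the test or formula behind 59, so several are tried.

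**Formula.** For the pooled normal approximation, let

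- A = √(2 × 0.12 × 0.88) = 0.4596
- B = √(0.20 × 0.80 + 0.04 × 0.96) = 0.4454
- n = [(z_alpha × A + 0.8416 × B) / 0.16]²
- power = Φ[(0.16 × √n − z_alpha × A) / B]
- continuity-corrected n = (n/4) × [1 + √(1 + 4/(n × 0.16))]²

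Exact power adds up the binomial probabilities of every pair of stricture counts that the test rejects.

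**Step 1. Can the printed level reproduce 59?** At one-sided 0.0005, z_alpha = 3.2905.

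- Pooled: n = [(3.2905 × 0.4596 + 0.8416 × 0.4454) / 0.16]² = 139.1, so 140 per arm.
- Pooled with continuity correction: 151.3, so 152.
- Exact Fisher: power first passes 80% at 139 per arm.
- Unpooled: 133. Arcsine: 125.

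No variant comes near 59. Even the smallest, 125 per arm, equals the planned total for both arms.

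**Step 2. Power of 59 per arm at the printed level.**

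- Pooled: Φ[(0.16 × √59 − 3.2905 × 0.4596) / 0.4454] = Φ(−0.636) = 26.2%.
- Exact Fisher: 18.8%. Exact chi-square: 22.7%.
- Other approximations: 17.7% (continuity-corrected), 29.8% (unpooled), 32.9% (arcsine).

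**Step 3. Does a 5% level reproduce 59?**

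| Level | n per arm for 80% power | Exact power at 59: Fisher | Exact power at 59: chi-square |
|---|---|---|---|
| One-sided 0.05 | 50 (pooled), 57 (exact Fisher), 60 (unpooled, corrected), 62 (pooled, corrected) | 82.3% | 88.5% |
| Two-sided 0.05 | 58 (arcsine), 59 (exact chi-square), 61 (unpooled) | 70.5% | 80.7% |
| One-sided 0.0005 | 125 to 152 | 18.8% | 22.7% |

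At 5% the figure is recovered within two patients by several methods. Some are one-sided and some two-sided, and the only exact hit, the two-sided chi-square enumeration, does not match the sidedness that the section states. The number 59 therefore identifies the 5% level but not its sidedness or the test.

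**The case against.** The strongest reply is that this is a misprint whose intended value is plain. The same sentence writes beta as a proportion, the abstract gives alpha as a proportion of 0.05, the statistics section plans a 95% interval, and 59 is recovered at 5% and nowhere near 0.05%. The correction changes no sample size, endpoint or procedure. All of that stands, and it limits the point to a wrong stated error rate.

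Four stronger readings are tempting, and the article does not support them:

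- *The trial is underpowered.* A reader might infer this from a power of about 20%. That figure holds only if 0.05% was really meant, and nothing in the article suggests it was.
- *The misprint is the trial's only threshold, so testing at 5% would breach the protocol.* The abstract also states an alpha, and testing at 5% would agree with it. Moreover, *Ethics* refers to a final protocol version 1.0 that is not shown, so it cannot be known whether the misprint is there or only in the article.
- *At the printed level the trial would almost certainly fail.* With power of 18.8% to 26.2%, it would miss the planned effect about 74-81% of the time. That is likely, but not near certain.
- *The sample size confirms a one-sided 5% test.* It does not, since two-sided calculations give 59 just as closely.

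The contradiction itself and the unsettled sidedness remain. Neither is a detail left to an analysis plan: one is a wrong printed number, and the other is a one-sided level set beside a two-sided interval.

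**Conclusion.** The point holds as a wrong printed significance level. With 20% against 4% and 59 per arm, one-sided 0.0005 gives about 19-26% power by the two exact tests and the pooled formula (17.7% to 32.9% over all approximations tried). Power of 80% would need about 139-152 per arm by exact Fisher and the pooled formulas, or 125 by the most lenient approximation. The stated alpha, power and sample size cannot all be true under any of these methods.

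That 5% was meant is an inference, though a strong one: it rests on the abstract and on the match with 59. Whether it was one-sided or two-sided cannot be settled from the article. The choice matters: exact power at 59 per arm is 82.3% to 88.5% one-sided, and 70.5% to 80.7% two-sided. All these figures take the article's assumed rates as given and count 59 evaluable patients in each arm.

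**What to change.** 1. In *Sample size calculation*, correct the significance level to 0.05 (5%).
2. Confirm from the original calculation whether that level is one-sided or two-sided. State level and sidedness identically in the abstract, the sample-size section and the statistics section. If one-sided is confirmed, explain there how the 95% interval, which corresponds to two-sided 5%, relates to the test.
3. Name the test or formula on which 59 per arm rests.
4. Check whether protocol version 1.0 carries the same misprint and, if so, correct it there too.

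The cost is a few lines of text. Correcting the misprint changes no patient numbers. *Trial status* reports 34 of the planned 125 patients enrolled, so the rule can be fixed on record well before the primary analysis.

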**Fig. 2 Fig2:**
[figure not shown]
Inclusion and treatment flow diagram

### Eligibility criteria

#### Inclusion criteria

Aged 20 to 80 yearsExpected curative resection for intrathoracic esophageal cancerRadical esophagectomy with reconstruction using a gastric conduit pulled upward through the posterior mediastinum or retrosternal routeEsophagogastric anastomosis at the cervical siteProven written informed consent

#### Exclusion criteria

The patients who cannot receive curative resection according to intraoperative findingsInability to undergo either the FEES or TS anastomosis safely according to intraoperative findings (just before cervical anastomosis)Interstitial pneumoniaUncontrollable diabetes mellitus that needs continuous intravenously administered insulinHistory of myocardial infarction or unstable angina pectoris within 6 monthsCardiac failure, New York Heart Association (NYHA) III degreeLiver cirrhosis, Child-Pugh class CActive hepatitisChronic renal failure requiring hemodialysis

### Randomization

After confirmation of the eligibility criteria, intraoperatively, registration is made by telephone to the Central Registry in Wakayama Medical University Hospital (WMUH). Patient randomization in each group is carried out using a series of consecutive numbers and assigned by the WMUH Central Registry. Patients are randomly assigned to either the FEES method group or the TS method group in a 1:1 ratio. Randomization has two stratification factors. The first one is the route of reconstruction (retrosternal or posterior mediastinal route), and the second one is the administration or absence of neoadjuvant chemotherapy. A clinical researcher performs the randomization using computer-generated, random blocks of 4 in the Central Registry of WMUH. Randomization will take place just before cervical anastomosis after feasibility confirmation of both the TS and the FEES method intraoperatively.

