### Surgical procedure

Patients with thoracic esophageal cancer undergo esophagectomy and mediastinal dissection with extensive lymphadenectomy. Patients undergo thoracoscopic esophagectomy in the prone position. Patients with severe pleural adhesions undergo a right thoracotomy via the fourth intercostal space. After the thoracic procedures are completed, the position of the patient is changed to supine and abdominal lymphadenectomy and gastric conduit reconstruction are performed using either an open laparotomy or laparoscopically. Cervical lymphadenectomy is performed in case of three-field lymphadenectomy. A 4-cm-wide gastric conduit is made along the greater curvature of the stomach using the linear-stapling device Echelon 60–3.5 (Ethicon Endo-Surgery, Cincinnati, OH, USA) in both groups. The gastric conduit is pulled upward to the cervical level through the retrosternal or posterior mediastinal route. At the left side of the neck, esophagogastric anastomosis is performed by either the TS or the FEES method. All operations, including anastomosis, are directed by one of two senior esophageal surgeons ([name] or [name]). They have experienced 40 cases or more of the TS method and 20 cases or more of the FEES method at the start of this RCT. They will perform both techniques equally.

The TS method is an end-to-end anastomosis using the 60-mm linear-stapling device Echelon 60–3.5 (Endo-Surgery, Cincinnati, OH, USA). The TS method procedure is composed of three steps: the first step is the firing of the linear stapler at the posterior wall of the cervical esophagus and the gastric conduit after inserting three or four suspension sutures. The second step is the firing of the linear stapler at half of the anterior wall after inserting the suspension sutures. The third step is the firing of the linear stapler at the remnant half of the anterior wall as in the second step. This technique has been described previously [4].

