## Trial status

The WMUH Institutional Review Board approved the final version of the protocol prior to the start of the study (approval number: 1943). The first patient was recruited on 30 January 2017. Currently, 34 patients have been enrolled in this trial and patient recruitment continues. The projected completion date for this trial is December 2019.

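### A single published block size of 4, in a one-centre trial with unblinded surgeons and an intraoperative entry judgement, makes up to about one third of allocations deducible

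*Protocol article*

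**What the plan says.** All of this is in the Protocol article.

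- **Block size and ratio (Randomization).** "A clinical researcher performs the randomization using computer-generated, random blocks of 4 in the Central Registry of WMUH". Also: "Patients are randomly assigned to either the FEES method group or the TS method group in a 1:1 ratio". One size is given, so each block holds two FEES and two TS assignments. I read "random" as the order within a block, since no second size is mentioned.
- **Strata (Randomization).** "Randomization has two stratification factors": reconstruction route and neoadjuvant chemotherapy, each with two levels. That makes four strata, and both factors are known before the call.
- **Concealment and timing (Randomization).** "registration is made by telephone to the Central Registry in Wakayama Medical University Hospital (WMUH"). "Randomization will take place just before cervical anastomosis after feasibility confirmation of both the TS and the FEES method intraoperatively".
- **Entry judgement (Exclusion criteria).** Patients who cannot safely have one or other anastomosis, on findings made immediately before the cervical anastomosis, are excluded. The article does not name who decides.
- **Setting and operators (Study objectives; Surgical procedure).** "This prospective, single-center, phase III trial aims to demonstrate the superiority of the FEES method over the TS method". "All operations, including anastomosis, are directed by one of two senior esophageal surgeons". Both surgeons use both techniques.
- **Recruitment (Trial status).** "Currently, 34 patients have been enrolled in this trial and patient recruitment continues". The planned total is 125 (Sample size calculation).

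**The concern.** A central telephone registry hides the list. It does not hide what past allocations imply about the next one. With a known block of 4, the fourth assignment always follows from the first three, and the third follows whenever the first two agree. A surgeon cannot be blinded to the anastomosis, and here all cases go through one small team.

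Predictability does harm only where someone can act on it. In this trial a judgement on whether the patient can be entered comes immediately before the call. If the next arm can be foreseen, that judgement could be influenced, even unconsciously, by how suitable the patient looks for that arm. Analysis by intention to treat cannot repair this, because a patient excluded before the call is never randomized.

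Few events are expected. At 59 per arm the planning rates give 59 × 0.20 = 11.8 strictures with TS and 59 × 0.04 = 2.4 with FEES, so a small shift in who fills the foreseeable slots could matter if the result is close.

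**Working it through.** **Inputs.** Block size 4, ratio 1:1, four strata (Randomization); 125 planned, 59 per arm, 20% vs 4% (Sample size calculation); 34 enrolled (Trial status). The article gives no predictability figure to reproduce. The 59 per arm serves only as a denominator below. A one-sided Fisher exact test at 0.05 has 82.3% power at 59 and first passes 80% at 57, so I use that test. I take the one-sided alpha as 0.05, as in the Abstract.

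**1. Everything known (block size, and all earlier allocations in the stratum).** Enumerate the 6 orders of two FEES and two TS.

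| Position in block | P(assignment certain) | P(best guess right) |
|---|---|---|
| 1 | 0 | 1/2 |
| 2 | 0 | 2/3 |
| 3 | 1/3 | 2/3 |
| 4 | 1 | 1 |
| Mean | (4/3)/4 = 33.3% | 17/24 = 70.8% |

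Without blocking the best guess is right 50% of the time. Simulating 125 patients in four strata with incomplete last blocks gives about 32% certain, or about 40 patients, for both an equal and a skewed stratum mix (the mix is assumed). For the 125 − 34 = 91 still to enrol, 91/3 is about 30.

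**2. No pooling.** Assume each surgeon directs half the cases at random, sees only those, and knows the position in the block. A surgeon is certain only after personally seeing both assignments of one arm.

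- Position 3: the first two agree (1/3) and both were this surgeon's cases (1/4), giving 1/12.
- Position 4: one arm has already been used twice, and both of those were this surgeon's cases, giving 1/4.
- Mean: (1/12 + 1/4)/4 = 1/12 = 8.3%. Of 91 patients, that is about 8.

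**3. Effect on the result** (one-sided Fisher, 59 per arm, TS vs FEES strictures).

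- *Extreme steering with no true effect.* Start from 12 vs 12. Of 30 deducible slots, 15 are in each arm, with 15 × 0.20 = 3 strictures expected in each set. Remove all 3 from FEES and double the 3 in TS: 15 vs 9, p = 0.13.
- *At the planned effect.* 12 vs 2 gives p = 0.004; 12 vs 4 gives 0.029; 12 vs 5 gives 0.057.
- *Near the threshold.* 10 vs 3 gives p = 0.037; 10 vs 4 gives 0.076.

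**4. Alternatives,** for an observer who sees every earlier allocation in the stratum and knows which sizes are in use, but not their order.

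| Scheme | Certain | Best guess right |
|---|---|---|
| Fixed 4 (complete blocks) | 33% | 71% |
| Random 4/6 | 5–6% | about 69% |
| Random 4/6/8 | about 2% | about 67% |

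The rows for random sizes are simulated with 31 patients per stratum (125/4). Repeating 4/6/8 with 23 per stratum (91/4) also gives about 2% and 67%.

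**The case against.** The strongest reply is that the one-third figure is an upper end. Each operation is directed by one of the two surgeons, so neither automatically sees every allocation. Nothing says that they were told the block size or that anyone keeps a tally in four strata. Who judges feasibility is not stated either. That it is the operating team is a reasonable inference from its being an intraoperative finding, but it remains an inference. All of this stands, and it is why the size is given as a range. Against it, two colleagues in one hospital can easily share what they have done, and the article itself makes the block size public with most patients still to come.

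Randomizing late, after both methods are confirmed feasible, is also a real safeguard. It narrows the discretion, since steering would mean declaring an anastomosis unsafe during the operation. It does not remove the discretion, because the judgement still comes before the call.

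A reader might go further and infer that one third of assignments are in fact known in advance, or that steering a few patients would change the result. The documents support neither. The first needs both the block size and pooled knowledge. The second fails in the extreme case with no true effect (p = 0.13), and at the planned effect it would take three extra FEES strictures to lose significance. Only a result already near the threshold turns on one event.

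Nor does the lack of a described log of exclusion reasons count against the plan, since an article commonly leaves that to the full protocol.

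**Conclusion.** The point holds as an avoidable design risk. Between about 8% of assignments (equal shares, no pooling, position in the block known) and about 33% (block size known, all earlier allocations shared) would be certain in advance. Among the 91 patients still to be enrolled, that is roughly 8 to 30. A surgeon unaware of the block size could be certain of none. The consequence is possible selection at the feasibility step, enough to tip a borderline comparison but not shown to overturn a clear one. The documents contain no evidence that selection has happened. The change is worth making because it is cheap and, on the stated recruitment status, would still cover 91/125 = 73% of patients.

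**What to change.** For the remaining patients, the Central Registry should generate a new list with randomly varying block sizes, for example 4, 6 and 8, within the same four strata. Neither the sizes nor their order should be disclosed to the surgical team or published before recruitment ends. Any block of 4 already open in a stratum should be completed before that stratum moves to the new list.

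The gain is mainly the loss of certainty: certain allocations fall from up to a third to about 2%. Guessing improves only modestly, from about 71% to about 67% correct, so some predictability remains.

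The cost is a new list and a short amendment. The largest possible imbalance within a stratum rises from 2 (a block of 4 stopped halfway) to 4 (a block of 8 stopped halfway). It could reach 2 + 4 = 6 if open blocks were abandoned, which is the reason to complete them first. The ratio, strata and sample size do not change.
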